**Objective:**

This trial aims to evaluate the efficacy of an anonymous online self-help tool for social anxiety that processes no personal data and has some disadvantages in terms of usability compared to an otherwise identical, nonanonymous evidence-based tool. Furthermore, the trial will investigate user preferences regarding the 2 program versions and evaluate the impact of these preferences on treatment outcomes.

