### Procedures

After receiving the study information and returning the signed informed consent form, the candidates will be screened for eligibility using the self-report measures described in the Instruments section. Participants will additionally be shown brief descriptions of both program versions during screening and asked to select their preferred option. If eligible, the participants will be assigned to a condition. The randomization will be performed in 2 steps to ensure correct condition allocation. In a first step, eligible candidates will be randomized with equal probability to either the randomization or preference condition. In a second step, the participants in the randomization condition will be randomized again with equal probability to one of the program versions (anonymous vs nonanonymous) regardless of previously expressed preference. The participants in the preference condition will be assigned to their preferred program version. Thus, the main effect of the treatment can be estimated, but it is also possible to explore preferences and their possible effects through the preference arm. The first randomization will be conducted using the built-in randomization tool in REDCap [28,29], where all the data will be collected, whereas the second randomization will be conducted by an external researcher with a randomization list created using randomly permutated blocks. An external researcher has to be involved in the randomization as REDCap can only perform one randomization per participant. The condition allocation will be unknown to investigators.

The intervention period, during which participants are asked to use the self-help program, will be 8 weeks. The duration of the study for 1 participant will be 24 weeks. There are 3 main measurement time points during this period: at the beginning (preassessment), after 8 weeks (postassessment), and after 24 weeks (follow-up assessment). In addition, there are 2 minor measurement points, after 3 and 6 weeks, where only preference and other measures unrelated to this part of the study will be assessed. The questionnaires will be sent out automatically through REDCap [28,29] via email at the corresponding time points.

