##### Preference

Preference will be assessed by presenting all participants with 2 approximately 150-word texts describing the 2 versions of the program. They will then be asked to indicate their preference and their preference strength by answering the question “How important is this choice to you?” on a 4-point Likert scale (1=“not important at all”; 4=“very important”), as done previously [52]. Participants are only forced to make a choice at preassessment to enable possible condition allocation for all participants that are randomized to the preference condition. At the remaining measurement points, participants can indicate that they have no preference.

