### Power Analysis

This study is powered regarding the primary outcome (composite score of the SPS and SIAS) and first study aim (whether anonymous digital interventions are less efficacious than conventional, nonanonymous programs). This means the comparison of the 2 versions in terms of reduction in SA symptoms in the randomized condition. As we expect a superiority of the nonanonymous version, a Cohen *d* value of 0.35 was used as the target effect size between groups as we considered smaller effects clinically insignificant. We conducted a power analysis for Cohen *d*=0.35 with an α level of .05 and a power of 0.80 for the time × group interaction. The sample size was determined using the ANOVA power Shiny app [55], which is based on the R programming environment [56], and the *Superpower* package for R (R Foundation for Statistical Computing). This app performs Monte Carlo simulations tailored to factorial experimental designs, allowing for interaction effects and comparisons across both within- and between-subject factors [55]. For the power analysis, we defined the randomized condition as a mixed 2 × 3 design with 2 program versions (between) and 3 time points (within). For means and SDs of the nonanonymous version, values from another trial with the same basic online program were taken [26], and for the anonymous version, the means were calculated using the aforementioned effect size. The SDs used were the same as in the nonanonymous version, and the correlation of within-subject factors was set at *r*=0.5. For SPS values with 2000 simulations, a total of 113 participants per condition are needed, and for SIAS values, 112 participants are needed per condition to reach 0.80 power for the interaction effect. Therefore, for the 2 randomized arms, 113 participants per arm will be recruited. Although we do not know beforehand how many participants will be in each of the 2 preference arms, we doubled the participants from the randomized arm for the power analysis, resulting in a total of 452 participants across all 4 arms.

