### Statistical Analysis

We will evaluate the differences in SA symptom change between the anonymous version (JOURNeY_A) and the nonanonymous version (JOURNeY_NonA) using linear mixed models with the posttreatment assessment as the confirmatory primary end point. Time will be used as the within-subject factor, and condition will be used as the between-subject factor. Fixed effects will be time, condition (JOURNeY_A or JOURNeY_NonA), and the intervention term; the random effect will be the intercept of each participant as every participant is expected to have a different prescore. This analysis accounts for the correlation of residual errors within participants and includes a treatment-by-time interaction term to assess differential symptom change over time [57]. Estimates for each time point will be derived from this model. We will conduct the analysis based on the intention-to-treat principle. The intention-to-treat analysis set consists of all participants in the randomized group regardless of any protocol violations. The inferences about overall program efficacy will only be made based on the randomized arm. For the exploratory preference analysis, appropriate methods such as multiple logistic regression, *t* tests, and chi-square tests will be used depending on the type of data. Comparisons will focus, for example, on participants who received their preferred treatment (preference match) versus those who did not (preference not matched). The amount and pattern of missing data will be reported, and results will be interpreted accordingly in a cautious manner. To allow for comparison across trials, we will also report the standardized mean differences (effect sizes).

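### The example contrast of matched with non-matched participants includes any version effect unless preferences split evenly, so on its own it does not isolate the impact of preference.

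*Protocol article*

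**What the plan says.** The abstract's Objective includes a plan to "evaluate the impact of these preferences on treatment outcomes". Statistical Analysis turns this into methods, with the choice left to the kind of variable: "For the exploratory preference analysis, appropriate methods such as multiple logistic regression, *t* tests, and chi-square tests will be used depending on the type of". As an example it names a comparison of "participants who received their preferred treatment (preference match) versus those who did not (preference not matched". The passage mentions neither version as a covariate nor stratification by version for this comparison.

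Procedures fixes how version relates to preference. First, "eligible candidates will be randomized with equal probability to either the randomization or preference condition". Those in the randomization condition are then "randomized again with equal probability to one of the program versions (anonymous vs nonanonymous) regardless of previously expressed preference". In the other condition, "The participants in the preference condition will be assigned to their preferred program version". The Preference section adds: "Participants are only forced to make a choice at preassessment". Match status is therefore defined at baseline for everyone.

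Power Analysis states the direction of the expected version effect, "As we expect a superiority of the nonanonymous version", and uses d=0.35 as the target. The preference split is left open under both Participants and Power Analysis.

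**The concern.** Match status is built from two things: what a person prefers and which version that person receives. When one version is preferred by the majority, most matched participants use the majority version and most non-matched participants use the other. A comparison of the two groups is then partly a comparison of versions. If the nonanonymous version is both more popular and more effective, matching looks helpful even when preference has no influence. If the anonymous version is more popular and less effective, matching looks harmful.

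The impact of preference is a stated objective, and the abstract's Conclusions link the findings to tailoring interventions to individual preferences. A version difference read as a preference effect would misinform that recommendation.

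**Working it through.** **Inputs.** There are 113 participants per randomized arm and 452 in total (Power Analysis; 4 × 113 = 452). The target version effect is d=0.35 (Power Analysis). Version is allocated 1:1 independently of preference, and everyone in the preference condition is matched (Procedures). The document gives no figure for the matched versus non-matched comparison, so there is none to reproduce. Assumptions: p, the share preferring the nonanonymous version, ranges from 0.5 to 0.9 (0.1 to 0.5 is the mirror image); SD 1; complete data; no true match effect.

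**Group sizes.** In the randomized arm the probability of a match is 0.5p + 0.5(1−p) = 0.5 for any p, so about 113 are matched and 113 are not. With the preference condition added, 113 + 226 = 339 are matched and 113 are not.

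**Version mix.** In the randomized arm, the share on the nonanonymous version is 0.5p/0.5 = p among the matched and 0.5(1−p)/0.5 = 1−p among the non-matched. The preference condition adds matched participants of whom a share p again use the nonanonymous version. The difference in mix is p − (1−p) = 2p−1, whether the arms are pooled or not. The share preferring each version is p in both groups in expectation, so the groups are balanced on preference itself.

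**What the crude contrast estimates.** Score the outcome so that higher is better. Let a be the version effect (nonanonymous minus anonymous) and m the match effect. Receiving the preferred version gains m + a for those who prefer the nonanonymous version and m − a for those who prefer the anonymous one. The average gain is

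p(m + a) + (1−p)(m − a) = m + (2p−1)a.

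**Size with m=0 and a=0.35.** The shift is (2p−1) × 0.35. The standard error is √(2/113) = 0.133 in the randomized arm and √(1/339 + 1/113) = 0.109 pooled. The two-sided rejection rate at 0.05 is Φ(shift/SE − 1.96) + Φ(−shift/SE − 1.96).

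| p | Shift (SD) | Rejection, randomized arm | Rejection, pooled |
|---|---|---|---|
| 0.5 | 0 | 5% | 5% |
| 0.6 | 0.07 | 8% | 10% |
| 0.7 | 0.14 | 18% | 25% |
| 0.8 | 0.21 | 35% | 49% |
| 0.9 | 0.28 | 56% | 73% |

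With a version effect of 0.20 in the randomized arm, the shift is 0.04 SD at p=0.6 (about 6% rejection) and 0.08 SD at p=0.7 (about 9%).

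**The contrast that removes version.** The version effect is a + m among those who prefer the nonanonymous version and a − m among those who prefer the anonymous one. Their difference, the version-by-preference interaction, is 2m, so half of it is m. The two preference groups have 226p and 226(1−p) members, each split evenly by version. The variance of the interaction is therefore 4/(226p) + 4/(226(1−p)) = 4/(226p(1−p)), and the SE of half of it is 1/√(226p(1−p)). That is 0.133 at p=0.5 and 0.166 at p=0.8.

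**Simulation check** (2000 runs per setting, version effect 0.35, no match effect). With a 70% or 80% majority, the crude contrast shifts by 0.14 and 0.21 SD. It rejects in 18% and 34% of runs in the randomized arm, and in 25% and 47% pooled. With version and baseline preference in the model, the shift is at most 0.002 SD in absolute value and rejection is 4.6% to 5.7% in every setting run.

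**The case against.** The strongest reply is that the article does not commit to a crude t test on the symptom score. The analysis is exploratory, the contrast is an example, the list of methods is open, and one listed method, multiple logistic regression, can carry covariates, though for a binary outcome. Study Design also names anonymity as a between-subject factor. This stands: a reader might infer that an unadjusted test is fixed, and the document does not go that far. It does name the contrast and t tests, with no version term, and a t test cannot adjust for version.

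A second reply concerns validity. Inside the randomized arm, match status is itself a fair coin flip, independent of preference and of other baseline characteristics. A reader might infer that the crude contrast is confounded and should not be reported at all. That is too strong, because it validly estimates receiving one's preferred version rather than the other one. The fault lies only in reading that quantity as the impact of preference.

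A third reply is that d=0.35 is the target below which effects were judged clinically insignificant, not a forecast, although superiority is expected. The preference split is unknown as well. The highest rejection rates need both the full 0.35 and a very lopsided split. This also stands.

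The Limitations section does not answer the point. It discusses characteristics linked to preference in the preference arm, whereas the version imbalance arises within the randomized arm too.

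**Conclusion.** The point holds as a matter of what the contrast estimates. A matched versus non-matched comparison without version in the model returns the match effect plus (2p−1) times the version effect, with or without the preference condition. It equals the match effect only if preferences split evenly or the versions are equally effective.

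The size cannot be predicted from the document, because neither p nor the true version effect is known. The tabulated shifts of 0.07 to 0.28 SD for p from 0.6 to 0.9 are illustrations that rest on the assumptions listed with the inputs. It would be wrong to infer that such rates are to be expected in this trial, or that the primary result is at risk. The version comparison among randomized participants is unaffected, and inferences about overall efficacy are confined to that arm.

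**What to change.** For the effect of preference on outcome, specify a model in the randomized arm with version, baseline preference and their interaction at each time point. Define the match effect as half the version-by-preference interaction at week 8, and report the version effect within each preference group beside it. If the crude matched versus non-matched contrast is also shown, label it as the effect of receiving the preferred version, including any version difference, and not as a preference effect.

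This takes a sentence or two in the analysis plan. The Results section says that no data have been analysed, so the change can still be made in advance; if such a model is already planned, stating so is enough. The price is precision when preferences are lopsided: at p=0.8 the SE is 0.166 instead of 0.133 (SD 1, complete data). At p=0.5 there is no loss.

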## Results

This study was funded in 2023, approved by the Cantonal Ethics Committee of Bern, Switzerland in May, 2024 and recruitment and data collection started in September 2024 and are ongoing as of the submission of this manuscript. As of the submission in May 2025, over 350 participants have been included in the study. Recruitment of the study was finished in September 2025 and data collection is projected to be finished in March 2026. No data has been analyzed yet.

## Discussion

### Principal Implications

Internet interventions can present a low-threshold and effective way of providing evidence-based care. However, low acceptance and use rates highlight the need to design interventions that directly address potential users’ concerns, particularly regarding data security and privacy. Freely accessible, evidence-based, and anonymous DMHIs could play a role in bridging the treatment gap for mental health care. This trial will assess whether an anonymous self-help tool for SA can be efficacious while addressing privacy concerns. In addition, the findings will provide insights into user preferences for anonymous versus nonanonymous versions.

### Limitations

One limitation of this trial is that all measures rely solely on self-report questionnaires without incorporating observer-based measures such as assessments by a mental health professional to evaluate clinical outcomes. As the goal is to evaluate the tool in its intended real-world use, no in-depth diagnostic interviews will be conducted to avoid compromising participants’ sense of anonymity. Second, the preference-based study arm may introduce confounding factors as user preferences might be linked to other characteristics that influence outcomes [58]. However, to still be able to make inferences about the overall efficacy, the randomization arm allows for direct comparison between the 2 program versions. Third, even in the anonymous conditions, participants provide intimate information through questionnaires, which may still affect their perception of anonymity. To mitigate this concern, we emphasize at various stages of participant interaction that only the program is anonymous, whereas the study itself does not guarantee complete anonymity. This approach strikes a balance between exploring the efficacy of an anonymous DMHI and monitoring changes in outcomes of interest. Fourth, it is plausible that individuals who place a particularly high value on anonymity may opt not to participate in the study due to the required disclosure of personal information during study procedures. As a result, this potentially relevant subgroup of the target population may be underrepresented in the sample, limiting the generalizability of the findings. Finally, the inability to accurately measure user engagement with the program is a problem. As there are no individual user data, the only indicator of adherence is the total amount of clicks registered on the website, which we will then divide by the total number of participants with access to the site during the trial to at least obtain some insights into user engagement.

### Future Directions

Future research should examine whether similar anonymous DMHIs can be effective for other psychological conditions. In addition, further investigating user characteristics that influence preferences and engagement could provide valuable insights into optimizing intervention design. Our study data may also offer initial indications of which users benefit most from an anonymous format.

### Conclusions

In conclusion, this trial will have important implications for future internet intervention development regarding degree of anonymity and possibilities of ensuring privacy. Freely and anonymously accessible DMHIs offer a low-threshold alternative to traditional approaches such as face-to-face psychotherapy. These interventions hold significant potential to extend evidence-based care to a wider audience, addressing unmet mental health needs and narrowing the mental health treatment gap.

## Abbreviations

DMHI: digital mental health intervention
IASMHS: Inventory of Attitudes Toward Seeking Mental Health Services
ISMI: Internalized Stigma of Mental Illness scale
LPFS-BF: Level of Personality Functioning Scale–Brief Form
PHQ-9: Patient Health Questionnaire–9
PRIVATE: Preference Research: Investigating Variations of Anonymity, Transparency, and Efficacy in Digital Health Applications
REDCap: Research Electronic Data Capture
SA: social anxiety
SAD: social anxiety disorder
SF-12: 12-Item Short Form Health Survey
SIAS: Social Interaction Anxiety Scale
SPS: Social Phobia Scale
